### Pilot data and Rationale

As a proof of principle for this proposed RCT, we assessed the effect of donepezil, over four months of treatment, on gait using an electronic walkway (GAITRite System) in six individuals with AD [38]. An increase in gait velocity and a reduction in gait variability were seen following cognitive enhancer treatment. In brief, participants with AD taking donepezil increased their mean gait velocity (G-vel) after one month (from 89.7 ± 11 to 106.9 ± 22, *p *= .045) under a single-tasking condition. These increases were sustained and improved after four months, suggesting a dose-response pattern as shown in Figure 2. Gait variability (G-var), assessed as coefficient of variation of stride time, decreased during follow-up (single-task from 22.3 to 11.30, *p *= .04). Since it is known that gait performance declines over time in older people, we compared these results with observational data from eight comparison individuals with MCI and found that the MCI group experienced a reduction of gait velocity over time. (Figure 2)

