### Measurements and Procedures

All participants will undergo a baseline, one month, and a final six-month assessment. Baseline gait assessment will occur within one week prior to starting donepezil (T0), with a second assessment occurring after 4 weeks of treatment at 5 mg of medication (T1). The third and final assessment will occur after participants have been on the full dose of donepezil, 10 mg, for a period of 5 months (T2), yielding a total period of follow-up of 6 months from baseline. Assessments at each of these time-points will include gait analysis, balance sway, and balance confidence as well as cognitive measurement of attention and executive function. Falls will be retrieved by phone interview as has been done in previous studies [47,48]. A timeline for the proposed study can be found in Figure 4.

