### Outcomes measures

#### Primary outcomes

1. Improvements in gait velocity (cm/second) at month six

2. Reduction in gait variability assessed as standard deviation (SD) and coefficient of variation (CoV) at month 6.

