### Randomisation

Once informed consent has been obtained and the baseline assessment has been completed, participants will be allocated to one of the two arms at a ratio of 1:1. Stratified randomization within strata based on fall history (0 falls, 1+ fall in past 12 months) will be performed. A block randomization by four will be applied to ensure a cumulative balance of participants between arms. The randomization sequence of the participants will be generated by a computer program and allocation to groups will be done with sequentially numbered opaque sealed envelopes. A professional bio-statistician not involved in recruitment and assessment will perform the randomization

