### Sample size determination

Sample size determination is based on our primary outcomes and using the values from the pilot data described above. We expect a 10% improvement in gait velocity (G-vel), measured in cm/s (effect size of 0.10 m/s, from 1.0 m/s to 1.10 m/s), and a reduction in gait variability (G-var) (stride time variability) of 10% as assessed by decreases in standard deviation and coefficient of variation. These expected changes are based on our preliminary data which showed that mean G-vel increased by 15% after one month of treatment and these changes were sustained and improved in the 4 months follow up [38]. In this study, we found that the mean stride time at usual gait was 1190 ± 266 milliseconds (ms), after one month of treatment was 1053 ± 178 ms, and after 4 month was 999 ± 112 ms. The absolute reduction of the mean group CoV was 11 points (from 22.4% to 11.3%). Therefore, it is reasonable to expect similar improvements in our proposed study with a larger sample. Thus, in order to detect a group reduction of variability of 10% with a type II error of 0.20, 69 participants in each arm will be needed for the final analysis; assuming a 5 percent drop-out rate (which was seen after 6 months in two previous studies testing medications on MCI), 75 per arm participants will need to be recruited. This sample will also allow the detection of a 10% difference in the mean scores of the ABC, which is considered clinically significant. While we will not have sufficient power for a definitive analysis of changes in fall rate or risk, we will be able to compare changes in the mean values of the primary outcomes with between-group differences in fall rate. This will add mechanistic evidence that changes in fall rate are due to changes in gait parameters, and will provide a point estimate needed for the sample size calculations for a future trial powered to detect a reduction in falls as a primary endpoint.

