### Statistical Analysis

Analyses will be performed according to an intention-to-treat principle. Baseline characteristics and gait parameters will be descriptively summarized using either means and standard deviations or frequencies and percentages, as appropriate. Comparisons of the changes in the mean balance confidence score will be assessed using *t*-test. The coefficient of variation [CoV = (SD/mean)*100] will be used to quantify gait variability. We will use linear regression to perform between-group comparisons using three data points (baseline, one month, six months) with baseline – 1 mo. corresponding to before treatment and 1 mo. – 6 mo. corresponding to treatment with donepezil. Linear regression models, both unadjusted and adjusted for age, sex, and history of falls, will be used for comparison of individual variables. Using the baseline value of an endpoint as a covariate is more powerful statistically than comparing the differences from baseline. The statistical significance of the results will be determined by Hochberg's variation of the Bonferroni procedure for multiple testing [65]. Two-sided *p *< 0.05 will be considered statistically significant. All calculations will be made using SPSS software package version 16.0 (SPSS Inc., Chicago, IL).

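### The analysis section labels the first month on study drug as pre-treatment, contradicting the visit schedule and leaving the reference point for the between-group comparison ambiguous

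*Protocol article*

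**What the plan says.** The Statistical Analysis section announces between-group comparisons by linear regression on the measurements from all three visits. It assigns the intervals between visits as follows: "with baseline – 1 mo. corresponding to before treatment and 1 mo. – 6 mo. corresponding to treatment with donepezil".

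The Measurements and Procedures section gives the schedule that those data points come from:

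- T0: "Baseline gait assessment will occur within one week prior to starting donepezil (T0"
- T1: "with a second assessment occurring after 4 weeks of treatment at 5 mg of medication (T1"
- T2: "after participants have been on the full dose of donepezil, 10 mg, for a period of 5 months (T2"

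The Randomisation section adds: "Once informed consent has been obtained and the baseline assessment has been completed, participants will be allocated to one of the two arms". No untreated or placebo run-in month is described anywhere.

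Two further statements bear on the analysis. The first primary outcome is "Improvements in gait velocity (cm/second) at month six", and the second, gait variability, is also set at month 6. Later in the same Statistical Analysis paragraph, the article says that adjusting for an endpoint's baseline value has more power than comparing changes from baseline.

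**The concern.** The interval label cannot be squared with the schedule. Participants are randomised after T0 and take study drug from then on, so T1 is a post-randomisation value measured on treatment in the donepezil arm. The label does not suit the placebo arm either, which has no donepezil period at any time. It describes a before-and-after layout, whereas the trial is a parallel-group comparison whose contrast begins at T0.

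This matters because the sentence is the only place where the article says how the three time points enter the between-group regression. An analyst who took it at face value would use T1 as the reference and attribute to donepezil only what happens between months 1 and 6. Two arms with equal change from month 1 to month 6 could then be reported as showing no effect, even if donepezil had worked by month 1 and the gain had been held.

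**Working it through.** **Step 1: the texts side by side**

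| Interval | Schedule (Measurements and Procedures; Randomisation) | Label (Statistical Analysis) |
|---|---|---|
| T0 to T1 | on study treatment, starting within a week of T0 | before treatment |
| T1 to T2 | on study treatment | treatment with donepezil |

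The first row is a direct contradiction. Reading the label as meaning before the full dose does not resolve it, because the schedule itself calls those four weeks treatment.

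**Step 2: what a literal reading removes**

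Write E1 for the donepezil-placebo difference at month 1 and E6 for the difference at month 6. Randomisation makes the expected difference at T0 zero.

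- Month-6 comparison adjusted for T0: estimates E6.
- Change from T1 to T2: estimates E6 − E1.

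If E1 has the same sign as E6, the second contrast is shifted toward zero by E1. If T1 is used as a covariate instead of being subtracted, the amount removed is E1 times the coefficient of T1.

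**Step 3: is an early effect plausible on the article's own data?**

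- Velocity (Pilot data and Rationale): "after one month (from 89.7 ± 11 to 106.9 ± 22". The gain is 106.9 − 89.7 = 17.2, and 17.2 / 89.7 = 19.2%. The Sample size determination section gives 15% for the same month.
- Mean stride time (Sample size determination): 1190, 1053 and 999 ms at baseline, 1 month and 4 months. The share present at month 1 is (1190 − 1053) / (1190 − 999) = 137 / 191 = 72%.

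**Step 4: illustrative power**

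Inputs from the article: 69 per arm analysed, 80% power, two-sided 0.05, and for velocity an "effect size of 0.10 m/s, from 1.0 m/s to 1.10 m/s", that is 10 cm/s.

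Assumptions: normal approximation; the same outcome SD for both contrasts; an SD back-solved so that 10 cm/s has 80% power, because the article does not state which SD it used.

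- d = (1.96 + 0.84) × √(2/69) = 0.477, about 0.48.
- Implied SD = 10 / 0.477 = 21.0 cm/s.
- With a share s of the effect present at T1, power = Φ(2.80 × (1 − s) − 1.96).

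| Share at month 1 | Effect left (cm/s) | Power |
|---|---|---|
| 0 | 10.0 | 80% |
| 30% | 7.0 | 50% |
| 50% | 5.0 | 29% |
| 72% | 2.8 | 12% |

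**Step 5: sensitivity to the SD assumption**

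For a T2 − T1 change score, the SD is 21.0 × √(2(1 − r)), where r is the within-person correlation. For a month-6 comparison adjusted for T0, it is 21.0 × √(1 − r²). Taking the 72% share and assumed values of r:

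| r | T2 − T1 change | Month 6 adjusted for T0 |
|---|---|---|
| 0.5 | 12% | 90% |
| 0.7 | 17% | 98% |
| 0.8 | 24% | >99% |
| 0.9 | 43% | >99% |

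**The case against.** The strongest reply is that a wrong label is not a wrong model. The article writes out no regression that subtracts T1 or uses it as the reference. Both primary outcomes are fixed at month 6, and the same paragraph favours the baseline value as covariate. A donepezil-placebo difference at month 6 adjusted for T0 loses nothing, whatever the interval is called. This stands. A reader might infer that the plan definitely discards the early drug effect and that the month-6 result is therefore biased; the document does not support that. The loss arises only if the period definition is applied literally.

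The reply also limits the numbers. The 72% share is for mean stride time, which is not a primary outcome, and comes from six participants with Alzheimer's disease treated open-label and followed for four months. The text gives no month-4 velocity value, so the corresponding share for velocity cannot be computed. The Follow-up section expects improvement after four months of treatment, which does not suggest a mainly early effect. The article ties 69 per arm to a 10% reduction in variability, whereas the illustration applies it to velocity. A reader might take 12% as the expected power, but it is the low end of a range that depends on the assumptions.

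None of this rescues the sentence itself. It is an affirmative statement at odds with the schedule, so it cannot be put down to the condensation of a journal article.

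**Conclusion.** The contradiction is certain: the Statistical Analysis section calls the first month pre-treatment, while the schedule and the randomisation procedure make it on-treatment. The consequence is conditional. The article supports two incompatible analyses, one that keeps any month-1 effect (month 6 adjusted for T0) and one that removes it (T1 as the pre-treatment reference), and the choice could change the trial's conclusion.

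How much would be lost under the second analysis is unknown, because the month-1 share of any effect in people with mild cognitive impairment is unknown. Under the stated assumptions, illustrative power ranges from about 50% to about 12% for shares of 30% to 72%. At the 72% share, a change score from T1 gives about 12% to 43% for correlations of 0.5 to 0.9. These figures show that the ambiguity is worth removing; they do not predict the trial's power.

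**What to change.** Reconcile the Statistical Analysis section with Measurements and Procedures and with Randomisation:

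- Delete the description of baseline to 1 month as before treatment.
- State that T0 is the only pre-treatment assessment and that T1 and T2 are both on-treatment.
- Define the primary contrast as the donepezil-placebo difference at month 6, adjusted for the T0 value of the endpoint.
- Report T1 as a secondary on-treatment time point, not as a reference or covariate for the primary contrast.

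This replaces a sentence of analysis wording and needs no extra participants, visits or data. It should be settled before unblinded data are seen, so that the choice between the two readings cannot depend on the results.

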## Anticipated problems and contingency plans

### Recording falls

Since falls tend to be forgotten or underreported, a strict definition of falls and a fall calendar will be implemented as "unintentionally coming to rest on the ground or other lower level." Participants will be asked to record any falls on the calendar every day and mail the completed calendar to the study office at the end of each month. Research assistants will verify the accuracy of all positive responses by phone interview, and will contact participants if calendars are more than two weeks late being mailed in. This strategy has been proven to be very effective for fall recording by others and us [47,57,58].

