### Pharmacological Treatment for Cognitive Problems

Cholinesterase inhibitors (ChEI), although modest in effect, are the most useful pharmacological treatment available for Alzheimer's Disease and vascular dementia [2,34]. Although not curative, their effects include memory stabilization and delays in functional decline and nursing home placement [2].

The molecular mechanism of action of ChEI is through increased cortical and hippocampal acetylcholine, an important neurotransmitter for memory regulation and neural plasticity. However, the mechanism of the clinical improvements in delaying functional decline is not well understood. One possible explanation may relate to not only the cognitive action of the drug, but also to subtle improvements in the motor function of these patients. Whether by direct effect or mediated through cognition, motor function improvement would consequently serve to stabilize mobility and delay functional decline. In Figure 1, we propose possible levels of action of ChEI on motor function and gait.

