#### Exclusion criteria

• Unable to understand English

• History of psychiatric illness within the last two years, including depression

• Parkinsonism or any neurological disorder with residual motor deficit (e.g. stroke, epilepsy)

• Musculoskeletal disorder detected by clinical examination which affects gait performance

• Active osteoarthritis affecting the lower limbs (America College of Rheumatology criteria [40-42])

• Chronic Bradycardia (baseline heart rate below 60 beats/minute)

• Use of psychotropic medication, which can affect motor performance (e.g. neuroleptics and benzodiazepines)

• Depression (score above 8/15 on the Geriatric Depression Scale – GDS [43,44]) since depression has been shown to reduce gait performance.

In order to increase generalizability of the results, the inclusion/exclusion criteria have been restricted to factors that can compromise study adherence and gait evaluation. The exclusions are to reduce the statistical noise introduced by specific diseases or disabilities that have strong known effects on gait. Exclusions will be based on a formal medical examination. The diagnosis of MCI is based on clinical criteria [15,45], which includes the presence of subjective memory complaints from the patient and family, objective memory impairment, preserved general intellectual function assessed clinically, absence of significant functional impairment, and absence of clinical dementia as assessed by a skilled geriatrician with extensive experience in a memory clinic setting. Objective memory impairment is operationalized, following the criteria set out by Petersen and colleagues [11]; demonstrated by memory impairment judged as beyond the normal range for age and education by a skilled geriatrician. Additionally, global cognition will be assessed using the Mini Mental State Examination (MMSE; scored 0–30), and the Montreal Cognitive Assessment (MoCA; scored 0–30, with higher scores indicating better performance). The MoCA test is a validated tool used to assess global cognition and was originally created to assist in the diagnosis of MCI [46]. In brief, when considering MMSE and MoCA performance in the same individual, a pattern of low MoCA score (<26) with normal MMSE score (>26) is associated with the diagnosis of MCI [46].

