#### Secondary outcomes

Between-group improvement in:

1. Balance confidence as evaluated by the Activities-Specific Balance Confidence Scale (ABC)

2. Balance sway, maximum saggital displacement, using a force platform (Bertec Inc.)

3. Attention measured with the Digit Span Test

4. Executive function using the Trail Making Test, parts A and B

5. Reduction of number of falls: The total number of falls by month 6 (T2) and proportion of participants who fall are also secondary outcome measures to be evaluated.

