#### Falls

A fall is defined as 'an unintentionally coming to rest on the ground, floor, or other lower level and not due to a seizure or an acute stroke [63]. Recurrent falls are defined as two or more events in a six-month period during the trial. An absolute reduction of 10 points in the rate of falls is expected in intervention group after six months of follow-up (20% in the control to 10% in the intervention). Because falls tend to be forgotten if no injuries are involved, a fall calendar enabling prospective assessment will be implemented [64]. At the baseline session, participants will receive a fall calendar and instructed in its use (i.e. they will be asked to record every day whether they have had a fall). Each monthly calendar page detaches along a perforation and becomes a postage-paid postcard addressed to the study office. Calendar pages each have a unique study ID number and no identifying information. If a calendar is not received by two weeks into the following month, or is missing or incomplete the research assistant will contact the participant by phone and together they will complete the page. Participants who indicate one or more fall will be contacted by study staff and interviewed about the circumstances and outcomes of the falls. These methods have been used locally in previous research [47,48].

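### Falls rest on self-recording by memory-impaired participants; a complete, on-time page showing no fall is never checked and no informant is named, so rates may be too low and the comparison modestly biased against donepezil

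*Protocol article*

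**What the plan says.** All places are in the protocol article.

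- **Role of falls.** Secondary outcomes: "The total number of falls by month 6 (T2) and proportion of participants who fall are also secondary outcome measures to be evaluated". The Falls section expects "20% in the control to 10% in the intervention". Sample size determination admits that power for falls is insufficient. It still plans to set fall differences beside the gait changes as mechanistic evidence, and to use the point estimate for sizing a future falls trial.
- **Who records.** Memory impairment is part of the entry diagnosis (text under Exclusion criteria): "demonstrated by memory impairment judged as beyond the normal range for age and education by a skilled geriatrician". Recording falls: "Participants will be asked to record any falls on the calendar every day and mail the completed calendar to the study office".
- **Forgetting is acknowledged.** Falls: "Because falls tend to be forgotten if no injuries are involved, a fall calendar enabling prospective assessment will be implemented".
- **What triggers contact.** Pages reporting a fall: "Research assistants will verify the accuracy of all positive responses by phone interview". For late, missing or incomplete pages, "the research assistant will contact the participant by phone and together they will complete the page". Neither Falls nor Recording falls describes contact after a complete, on-time page with no fall.
- **A different description.** Measurements and Procedures says that falls are obtained by telephone interview and does not mention the calendar.
- **The drug and cognition.** The mechanistic hypothesis is that gait and balance improve through attention and executive function. Of cholinesterase inhibitors in Alzheimer's disease and vascular dementia the article says that "their effects include memory stabilization and delays in functional decline and nursing home placement". Of their use in MCI it says that the cognitive effect in a recent randomised trial was weak and of doubtful clinical importance.

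**The concern.** The plan names forgetting as a problem, but its remedy depends on the impaired faculty: the participant must remember the fall and remember to write it down. A forgotten fall can leave a page that looks complete and negative, and that is the one kind of page with no check. Pages rebuilt by phone draw on the same person's memory. A fall early in a month may by then be about six weeks old (a month of roughly four weeks plus the two-week wait). No family member or other informant is named as a source, although the MCI diagnosis already uses complaints from the family.

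Two consequences follow. Lost falls lower the observed rates in both arms. And if the mechanistic hypothesis is right, donepezil could improve recording itself, so that capture is better on the active arm. Blinding does not prevent this, because the drug effect would cause it. The bias would run against donepezil. Low power is no answer here, since the estimate itself is what the plan wants to carry forward.

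**Working it through.** **Inputs.** From the article: expected proportions falling of 20% (control) and 10% (donepezil) by six months; 69 per arm at the final analysis; two-sided 0.05; 1:1 allocation. Assumed: the share of fallers captured, *s*. The article gives no capture figures, so a range is shown.

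**The plan's own position.** For 20% v 10% with 69 per arm, a two-sided comparison of proportions has power 0.375, and 80% power needs 199 per arm. This agrees with the statement that power for falls is insufficient.

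**Model.** Observed proportion = true proportion × *s*. Hence observed risk ratio (RR) = true RR × (*s* on donepezil ÷ *s* on placebo).

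**Equal capture in both arms, true 20% v 10%.** The RR stays at 0.50, but rates and power fall:

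| Capture | Observed | Power at 69 per arm | N per arm for 80% power |
|---|---|---|---|
| 100% | 20% v 10% | 0.375 | 199 |
| 80% | 16% v 8% | 0.30 | 258 |
| 70% | 14% v 7% | 0.27 | 300 |
| 60% | 12% v 6% | 0.23 | 356 |

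**Unequal capture (placebo / donepezil).**

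| Capture | True 20% v 10% | RR | True 20% v 20% | RR |
|---|---|---|---|---|
| 80% / 90% | 16% v 9% | 0.56 | 16% v 18% | 1.13 |
| 70% / 80% | 14% v 8% | 0.57 | 14% v 16% | 1.14 |
| 60% / 80% | 12% v 8% | 0.67 | 12% v 16% | 1.33 |

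Example at 70% / 80%: 0.20 × 0.70 = 0.14 and 0.10 × 0.80 = 0.08, so 0.08 ÷ 0.14 = 0.57 and the difference is 6 points instead of 10. With no effect, 0.20 × 0.80 = 0.16 and 0.16 ÷ 0.14 = 1.14.

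**Effect on sizing a later trial.** N per arm = [1.96 √(2p̄(1−p̄)) + 0.842 √(p₁(1−p₁) + p₂(1−p₂))]² ÷ (p₁−p₂)². For 14% v 8%, p̄ = 0.11: (1.96 × 0.4425 + 0.842 × 0.4405)² ÷ 0.06² = 1.533 ÷ 0.0036, or 426. The same formula gives 199 for 20% v 10%, and 300 for 14% v 7%.

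**What a reversal needs.** The observed RR exceeds 1 only if the capture ratio exceeds 1 ÷ true RR. At 20% v 10% that is 0.20 ÷ 0.10 = 2.0. At 20% v 15% it is 0.20 ÷ 0.15 = 1.33.

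**Chance of a false significant result.** With no true effect and 69 per arm, it is about 5% at 70% / 80% (no real inflation) and about 10% at 60% / 80%. The harm is to the estimate more than to the test.

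**The case against.** The plan anticipates forgetting and answers it with prospective daily recording, monthly return and phone follow-up, citing its own and others' experience. Late, missing and incomplete pages are chased, and those calls can add falls. If every day needs an entry, as the Falls section suggests, a participant who neglects the calendar leaves blanks that trigger a call, and the gap shrinks to days wrongly marked as free of falls. All of this stands, although the wording in Recording falls can also be read as asking only for falls to be marked, in which case a blank page counts as negative. A reader might infer that only reported falls are checked and that forgotten falls are never recovered. The documents do not support that.

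The capture figures are invented, and no source shows that a weak cognitive effect would move capture by ten points. This stands: they illustrate direction and scale only. The memory benefit quoted above concerns dementia, not MCI. One capture factor per arm is also crude, since someone who falls repeatedly has several chances of being counted. In a trial of this size, 14% v 16% is about 10 v 11 people of 69 (0.14 × 69 = 9.7; 0.16 × 69 = 11.0), well inside an interval of about ±12 points (1.96 × √[(0.14 × 0.86 + 0.16 × 0.84) ÷ 69] = 0.119).

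The article is condensed, and a fuller protocol may provide for informants. That is possible. But the article sets out fall recording in detail, in two places, and lists the triggers for contact, so the gap is visible in what it does state.

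**Conclusion.** The point holds in limited form. A complete, on-time page with no fall is accepted unchecked from people selected for memory impairment, and no second source is named. Under-recording lowers the fall rates. Recording that differs by arm is plausible under the trial's own mechanism and would bias the falls comparison modestly against donepezil: RR 0.57 instead of 0.50 at assumed capture of 70% v 80%, or 1.14 instead of 1.00 if there is no effect. A later trial sized on 14% v 8% would need 426 per arm, against 199 at 20% v 10%. These sizes rest wholly on the assumed capture rates.

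A reader might go further and infer that donepezil will appear to cause falls. That needs a true effect that is nil or small relative to the capture ratio. At the plan's 20% v 10% it needs capture on donepezil more than twice that on placebo, which sits badly with a cognitive effect that the article calls weak. The gait outcomes are measured by instrument and are not touched.

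**What to change.** 1. In Falls and Recording falls, name at baseline a family member or other informant, where available, to complete the calendar with the participant and to join calls about late or incomplete pages, by the same rule in both arms.
2. At the one-month and six-month visits, ask every participant and informant about unrecorded falls, including those whose pages were all negative. Treat this as a supplementary check: keep the calendar-based count as the main source and report falls added at visits separately by arm.
3. Record informant availability by arm.
4. Reconcile Measurements and Procedures (telephone interview) with Falls and Recording falls (calendar with triggered calls), and say whether a blank day makes a page incomplete.

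**Cost.** Revised calendar wording, a consent line for the informant and a few minutes at visits already scheduled. Some participants will have no informant. Recall at the six-month visit reaches back five months and still depends partly on the participant's memory, so it cannot replace the calendar or fully remove a difference in capture between arms.
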